#### Economic analyses

Over the intervention period, incremental effects on the primary outcome will be compared with incremental costs to inform within-trial cost effectiveness and extended to secondary outcomes where appropriate for cost effectiveness analysis beyond study. Within the trial, incremental costs and effects under uncertainty and their bivariate distribution will be estimated with bootstrapping (re-sampling with replacement) on paired centre level costs and effects (with centre level effects in turn bootstrapping on individual child effects). This approach allows robust estimation of the joint distribution under uncertainty and for the relationship (covariance) between costs and effects observed within the study and the uncertainty of effects across children within centres [64]. Standard summary measures for cost-effectiveness analysis, including net benefit curves, cost-effectiveness acceptability curves, and expected net loss curves and frontiers will be presented to best inform societal decision makers of the net benefit of the intervention and value of future research [65, 66].

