### Participant recruitment and eligibility criteria

The sampling frame comprised ECEC centres located in areas of disadvantage in NSW, Australia, according to the area location indices for socio-economic disadvantage (SEIFA) [38]. Centres were eligible if they were located in an area with a SEIFA index of relative socioeconomic disadvantage of less than or equal to 5 (lowest 50 %) [38] and had a minimum enrolment of five eligible consenting children. From the 74 eligible ECEC centres, 57 centres were approached and 44 centres were successfully recruited. One centre withdrew from the study due to not having the minimum number of consenting children (*n* = 3).

Children were eligible to participate in the evaluation components of the study if they were 3 years old, or turning 3 before the start of the intervention; attended at least 2 days a week at a participating ECEC centre; and were not likely to be enrolled in primary school the following year. All parents/caregivers of eligible children received a participant information sheet and a URL YouTube link to a recruitment video and were invited to provide written consent to participate. All educators working with 3 year olds in the ECEC centres were also invited to take part in the study and provide written consent to participation. Educators who are employed in centre-based ECEC services across Australia, and who are responsible for a group of children, are required by national regulations to hold at least a 12-month vocational qualification to work with children or be enrolled to complete such a vocational qualification [39]. Recruitment began in January 2015 and was completed in June 2015.

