### Power and sample size

Sample size and power estimates were based on the formula proposed by Murray [33] to adjust for a clustered (nested) cohort design. It is recommended that sample size estimates be based on the *a priori* minimum acceptable difference between groups to be considered meaningful [40–42]. Based on our experience and the changes observed in our pilot studies for accelerometer-based physical activity, we estimated this minimum acceptable difference to be 45 mins/day of total physical activity, which translates to an effect size (Cohen’s d) of 0.4. The 6-month Jump Start pilot [14] resulted in a Cohen’s *d* = 0.4 for counts per min, and the 6-month Jump Start translational pilot resulted in a Cohen’s *d* = 0.39 for percentage of time spent in LPA [43]. We therefore concluded that achieving an effect size ≥ 0.4 was realistic and our multi-component intervention strategies, with an increased intervention length and intensity compared to our pilot studies, would be expected to produce an effect size similar to or greater than these studies. For a two-tailed alpha = 0.05 and an intraclass correlation (ICC) of 0.01–0.05 our proposed sample size of 608 participants (304 per group) provides approximately 86 % power to detect an intervention effect of 0.4 or greater for the ICC range proposed.

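### The two-stage cost-effectiveness bootstrap, as written, counts child variation within centres almost twice and widens the effect standard error by about 24 to 35 % at the planned ICCs

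*Protocol article*

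**What the plan says.** The Economic analyses section of the protocol article sets out the resampling in two steps, the second nested inside the first: "bootstrapping (re-sampling with replacement) on paired centre level costs and effects (with centre level effects in turn bootstrapping on individual child effects". The reason given for the second step is to allow for "the uncertainty of effects across children within centres", and the section describes the resulting joint distribution as robustly estimated. It cites a reference for the approach, but neither this section nor any other mentions shrinkage or another adjustment to the child-level step.

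The outputs are net benefit curves and acceptability curves, and "expected net loss curves and frontiers will be presented to best inform societal decision makers", covering both the net benefit of the intervention and the value of future research.

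**The concern.** The second stage is meant to bring in uncertainty that the first stage already contains. A centre's observed mean effect varies for two reasons: centres truly differ, and each mean rests on a finite number of children. The spread of observed centre means reflects both, so resampling them with replacement carries both into the bootstrap distribution. Redrawing children with replacement inside each drawn centre then adds the child-level part again.

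The error is largest when the ICC is low, because child variation then makes up most of the variance of a centre mean. That is the range this trial planned for.

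Excess width is not harmlessly conservative here. Acceptability probabilities and expected net loss are direct functions of the bootstrap spread. Too much spread moves acceptability towards 50 % and inflates expected net loss, which makes further research look more valuable than the data warrant.

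**Working it through.** The protocol gives no figure for the bootstrap's uncertainty, so there is none to reproduce. The check derives what the stated scheme produces.

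**Inputs**
- Children: "our proposed sample size of 608 participants (304 per group" (Power and sample size).
- Clustering: "an intraclass correlation (ICC) of 0.01–0.05" (same section).
- Centres: "57 centres were approached and 44 centres were successfully recruited" (Participant recruitment and eligibility criteria), so 22 per arm. One later withdrew.
- Children per centre: m = 608/44 = 13.8. With 43 centres, 608/43 = 14.1.
- Assumption: equal centre sizes.

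**Formulas.** Set total variance to 1, so the between-centre variance is b = ICC and the within-centre variance is w = 1 − ICC.
- Correct variance per centre mean: T = b + w/m.
- Variance added by redrawing m children with replacement: E = (w/m)(m − 1)/m.
- Ratio of standard errors with many centres: √(1 + E/T).
- A centre-only bootstrap with k centres per arm has expected variance (k − 1)/k times the correct one. Against the true standard error, the two-stage ratio is therefore √((k − 1)/k + E/T).

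**Numbers (m = 13.8, k = 22)**

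| ICC | T | E | Variance ratio 1 + E/T | SE ratio, many centres | SE ratio vs true SE, k = 22 |
|---|---|---|---|---|---|
| 0.01 | 0.0816 | 0.0665 | 1.81 | 1.35 | 1.33 |
| 0.03 | 0.1002 | 0.0651 | 1.65 | 1.28 | 1.27 |
| 0.05 | 0.1188 | 0.0638 | 1.54 | 1.24 | 1.22 |

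With 43 centres the many-centre ratios are 1.35 (ICC 0.01) and 1.24 (ICC 0.05). Centre-only resampling gives √(21/22) = 0.977 of the true standard error, which is nearly unbiased.

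**Simulation** (22 centres per arm, 14 children each)
- The two-stage SE was 1.33 (ICC 0.01) and 1.22 (ICC 0.05) times the true SE. Relative to the centre-only bootstrap it was 1.36 and 1.25 times.
- With unequal centre sizes (5 to 23 children) the ratios to centre-only were 1.35 and 1.26.
- With matched pairs resampled, and half the centre variance shared within pairs, the ratios to pair-only resampling were 1.38 and 1.30.

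Losing 20 to 30 % of children leaves the many-centre ratio at 1.35 (ICC 0.01) and about 1.26 (ICC 0.05). Across separate simulation runs with 21 or 22 centres per arm, nominal 95 % intervals from the two-stage scheme covered about 96 to 99 %.

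**Illustration of the consequence.** Assume that effect uncertainty dominates net benefit and that mean net benefit is u correct standard errors above zero. Neither assumption comes from the protocol. Expected net loss in SE units is L(u) = φ(u) − u·Φ(−u), and with the SE inflated by a factor s it becomes s·L(u/s).
- At u = 1 and s = 1.24, the probability of being cost-effective falls from Φ(1) = 0.84 to Φ(1/1.24) = 0.79. Expected loss rises from 0.0833 to 0.1474, or 77 %.
- At s = 1.24 the rise is 24 % when u = 0 and 44 % when u = 0.5. It exceeds 77 % when u = 2.

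**The case against.** The strongest reply is that this is one parenthesis in a condensed article. It cites a method that is not at hand, and that method could include a shrinkage correction. The gloss about replacement also sits beside the centre stage only. A corrected two-stage bootstrap would be compatible with the wording. This stands as a reason to let the authors answer by stating a correction. It does not change what the text describes, which is bootstrapping at both levels with no adjustment, justified by a purpose the first stage already serves.

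Several points on size also stand:
- The 24 to 35 % is the many-centre figure. Against the true SE with 22 centres per arm it is 22 to 33 %.
- The ICC range is a planning assumption. By the same formula the many-centre excess falls to 17 % at ICC 0.10 and 10 % at ICC 0.20, and no ICC is given for the secondary outcomes to which the analysis may extend.
- Costs are resampled only at centre level and are not double counted. If costs made up half the net-benefit variance, with no covariance, the excess in the net-benefit SE at ICC 0.05 would be √(1 + 0.5 × 0.537) − 1 = 13 %.
- The 77 % rise in expected loss is one point on a wide range.
- Mean cost, mean effect, mean net benefit and the primary hypothesis test are untouched.
- Centre-only resampling is not exactly nominal either: its 95 % intervals cover about 93 to 94 % with 21 or 22 centres per arm. That is an ordinary small-sample shortfall and no reason to double count.

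**Conclusion.** The concern holds. As written, the scheme counts child variation within centres almost twice. The variance of the effect is overstated by about 54 to 81 % and its standard error by about 24 to 35 % over the planned ICC range, or 22 to 33 % against the true SE with 22 centres per arm. These figures assume about 14 children per centre, the ICCs used for the power calculation, and no correction at the child stage. Unequal centre sizes and moderate loss of children change them little, and higher ICCs reduce them. The effect on acceptability and expected net loss runs in a known direction, but its size depends on willingness to pay and on the share of uncertainty due to costs. This is a secondary analysis, but its main outputs depend on this spread, so the scheme should be corrected.

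**What to change.** Resample whole centres with replacement, carrying each drawn centre's cost and all its children's effects unchanged, and drop the child-level redraw. Because centres were randomised within matched pairs (Randomisation section), the pair is the natural resampling unit. That follows from the design and is separate from the double counting. The section should also say whether the pairing it mentions means cost with effect or matched centres.

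If two stages are preferred, apply a shrinkage correction to the centre means with standardised child residuals, and say so in the text. If the cited method already does this, one sentence stating it settles the point.

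The cost is a change of code or wording. No new data are needed, and the centre-only version is simpler than the present scheme.

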## Discussion

This paper presents the study protocols for the *Jump Start* intervention. This 18-month intervention is unique in its approach to supporting the health behaviours of children living in disadvantaged communities, drawing on evidence and lessons learnt from pilot studies [28, 30, 31, 35, 36] and fostering strong collaborative partnerships between the ECEC sector and multi-disciplinary research team. To the authors’ knowledge, *Jump Start* is one of the first interventions that uses a comprehensive multi-component, multi-setting approach to address the low levels of physical activity and gross motor skill proficiency among preschool-aged children in disadvantaged communities [1].

Targeting young children from disadvantaged communities is important because they typically have limited access to physical activity opportunities, and reduced physical activity levels and gross motor skill proficiency [67–69]. Through the *Jump Start* intervention, we expect to increase total physical activity by a minimum of 45 min/day, 20 min of which will be MVPA. We expect that large and meaningful benefits will flow into other areas of health and development, as evidence shows increases of this magnitude are associated with significant declines in adiposity and significant increases in bone health at ages 8 and 11 years [17]. This approach may also improve behavioural self-regulation skills in this age group, which are better predictors of school readiness than IQ or entry-level literacy or numeracy skills [70].

*Jump Start* will also enhance the quality of early childhood education and care at a crucial time in children’s lives when the architecture of the developing brain is most open to the influences of experiences and when health inequality gaps are smallest. Benefits also accrue for parents and educators. *Jump Start* focuses on capacity building and enhancing the knowledge and self-efficacy of all participating ECEC educators in teaching gross motor skills and integrating physical activity into daily routines through targeted professional learning and on-going support.

In addition, the *Jump Start* intervention, if effective in improving physical activity and educational outcomes of disadvantaged children, can reduce social system costs and benefit the economy. While $1 invested in effective education has shown a long term return of $1.50–$3 across populations, a benefit ratio for $1 of effective education in disadvantaged children (the target population of this intervention) has been estimated at $17 [71]. If children enter primary school with greater skills or learning in our focus areas (motor development, physical activity, behavioural self-regulation) they are less likely to repeat grades or drop out of school, and more likely to enrol in post-secondary education [71, 72].

The *Jump Start* intervention is a unique program to address low levels of physical activity and gross motor skill proficiency, and support healthy lifestyle behaviours among young children in disadvantaged communities. If shown to be efficacious, the *Jump Start* approach can be expected to have implications for ECEC policies and practices, and ultimately a positive effect on the health and development across the life course.

## Abbreviations

ATSI: Aboriginal and Torres Strait Islander
BMI: Body mass index
CALD: Cultural and linguistic diversity
CONSORT: Consolidated standards of reporting trials
ECEC: Early childhood education and care
EYLF: Early years learning framework
GMS: Gross motor skills
ICC: Intraclass correlation
LMVPA: Light-moderate-vigorous physical activity
MVPA: Moderate-vigorous physical activity
NQS: National quality standards
OECD: Organisation for economic co-operation and development
PA: Physical activity
RCT: Randomised cluster trial
SD: Standard deviation
SEIFA: Socio-economic indexes for areas
SES: Socioeconomic status
SOS: Speed of sound
TGMD-2: Test of gross motor development
